## Abstract

**Introduction:**

There is concern regarding suicidal behaviour risk during selective serotonin reuptake inhibitor (SSRI) treatment among the young. A clinically useful model for predicting suicidal behaviour risk should have high predictive performance in terms of discrimination and calibration; transparency and ease of implementation are desirable.

**Methods and analysis:**

Using Swedish national registers, we will identify individuals initiating an SSRI aged 8–24 years 2007–2020. We will develop: (A) a model based on a broad set of predictors, and (B) a model based on a restricted set of predictors. For the broad predictor model, we will consider an ensemble of four base models: XGBoost (XG), neural net (NN), elastic net logistic regression (EN) and support vector machine (SVM). The predictors with the greatest contribution to predictive performance in the base models will be determined. For the restricted predictor model, clinical input will be used to select predictors based on the top predictors in the broad model, and inputted in each of the XG, NN, EN and SVM models. If any show superiority in predictive performance as defined by the area under the receiver-operator curve, this model will be selected as the final model; otherwise, the EN model will be selected. The training and testing samples will consist of data from 2007 to 2017 and from 2018 to 2020, respectively. We will additionally assess the final model performance in individuals receiving a depression diagnosis within 90 days before SSRI initiation.

The aims are to (A) develop a model predicting suicidal behaviour risk after SSRI initiation among children and youths, using machine learning methods, and (B) develop a model with a restricted set of predictors, favouring transparency and scalability.

**Ethics and dissemination:**

The research is approved by the Swedish Ethical Review Authority (2020–06540). We will disseminate findings by publishing in peer-reviewed open-access journals, and presenting at international conferences.

STRENGTHS AND LIMITATIONS OF THIS STUDYThe study will make use of a large and nationally representative data linkage of Swedish registers, covering virtually any Swedish resident who initiated selective serotonin reuptake inhibitor treatment during the study period.We will compare different machine learning models and approaches to selecting predictors, in order to explore the performance of an ensemble prediction model using machine learning methods in Swedish register data, and to develop a clinically applicable model with a restricted set of predictors where transparency and scalability are favoured.We will follow the Transparent Reporting of a multivariable prediction model for Individual Prognosis or Diagnosis (TRIPOD) guidelines in the reporting of our study results.The prediction models will be developed and validated in Swedish register data, and the extent to which they can be generalised is unclear: further work to validate the model in other national contexts will be necessary.

## Introduction

Suicide is among the leading causes of death among younger individuals.^1^ Meanwhile, suicide is often accompanied, and/or driven, by underlying psychiatric disorders—mood disorders in particular.^1^ Compared with the general population, depressed individuals have been found to have around a 20 times higher rate of suicide.^2^ Antidepressants are the main pharmacological treatment option for mood disorders—taken by over 12% of the population in the USA^3^—and selective serotonin reuptake inhibitors (SSRIs) are the most common antidepressant type in many countries.^3 4^ They are also the first-line pharmacological treatment for depression among children and adolescents in many countries, including in Sweden.^5^

Although commonly prescribed, there are concerns about the risk of suicide during SSRI treatment among children and adolescents, based on evidence from randomised control trials^6^ and observational studies.^7^ Questions on whether and in what circumstances this association indicates causation remain.^7^ Regardless of causality, producing a model to assess which individuals, out of those initiating an SSRI, are more or less likely to engage in suicidal behaviour could be an important aid in clinical decision-making in terms of determining which individuals will require more clinical oversight. Models that predict suicidal behaviour risk within short time frames are expected to be most clinically relevant.^8^ However, applying a risk prediction model represents only one aspect of a more comprehensive approach necessary to prevent suicidal behaviour.^9^

Many studies have developed prediction models for suicide or suicidal behaviour in different populations.^10^ However, no prior study has predicted suicidal behaviour among children, adolescents and young adults who initiate an SSRI.

Some previous prediction studies have incorporated a wide variety of available predictors in order to harness the potential of large routinely collected electronic health records.^11–13^ For example, a previous study using Swedish register data was able to predict suicide following a psychiatric inpatient visit with a relatively high level of discrimination performance.^12^ However, this approach results in large models that may not be practical to implement in real-life settings where clinicians do not have access to routinely collected data. In such a setting, a clinician might want a restricted number of predictors to input into a risk prediction model that is simple, scalable and transparently operationalised – for example as an online tool.^14 15^ Previous research also suggests that clinicians want to understand why specific individuals are assigned a specific risk score, in particular when the risk classification is counterintuitive,^16^ which may favour the latter type of model.

Given the high baseline risk among many under consideration for SSRI-treatment, and the possibility of an elevated risk observed early during treatment,^8^ we therefore aim to predict the risk of suicidal behaviour within 30 days of SSRI initiation in a population of children, adolescents and young adults, aged 8–24 years. We do this in two ways: by applying a broad predictor set and relatively complex ensemble machine-learning approach, as compared with a clinically informed approach using a restricted set of predictors and favouring a more transparent model. It should be noted that our aim is not to determine which individuals should or should not be treated with an SSRI, but to identify whom, among those who do initiate an SSRI, is at particularly elevated risk of suicidal behaviour. Given that children under age 18 are routinely treated for psychiatric disorders in specialist care in Sweden, we expect our model to be mainly applicable to a specialist care setting.

### Research aim

To predict the risk of suicidal behaviour among young individuals within 30 days of SSRI initiation, with a secondary analysis considering events within 90 days of initiation. We will use a two-stage approach in order to: (A) explore the performance of an ensemble prediction model using machine learning methods in Swedish register data, and to (B) develop a clinically applicable model with a restricted set of predictors where transparency and scalability is favoured.

## Methods and analysis

We will use a two-stage approach to produce a prediction model:

*Broad predictor model*: a relatively broad set of predictors is included in a number of different machine learning base models, the predictions of which are then combined to produce an ensemble prediction.*Restricted predictor model:* a restricted set of top predictors identified from model A is included in a number of different machine learning models, which are compared in terms of predictive performance and transparency.

### Data source

We will obtain data from Swedish national registers, where linkage of records is based on unique personal identification numbers.^17^ The Prescribed Drug Register—which includes all dispensed medications since July 2005—will be used to extract information on psychotropic medication receipt, including the initiation of SSRI medication.^18^ The Total Population Register, which includes demographic information on Swedish residents since 1968, will be used to extract sex and country of birth for an individual.^19^ The National Patient Register, documenting discharge diagnoses from inpatient and outpatient care since 1973 and 2001, respectively, will be used for information on psychiatric diagnoses, including suicide attempts.^20^ The Cause of Death Register will be used to extract information on death by suicide.^21^ The Longitudinal Integrated Database for Health Insurance and Labour Market Studies register—which includes information on socioeconomic variables for individuals aged 16 or above since 1990 and for those aged 15 or above since 2010—will be used to extract information on the highest commenced education between individuals and their parents.^22^ The multigeneration register, including information on family relations,^23^ will be used to link individuals to their parents, whose history of psychiatric disease and of death by suicide can then be extracted from the National Patient Register and Cause of Death register, respectively.

### Inclusion criteria

We will include all individuals aged 8–24 years who were born in Sweden and who initiated an SSRI after a wash-out period of 365 days free from any antidepressants during 1 January 2007 to 31 December 2020. The first initiation event per individual will be included.

### Patient and public involvement

We have not involved patients in planning or executing this study. The research is based on observational register data, meaning no participant recruitment was necessary.

### Outcome ascertainment

Based on previous work, we will consider any International Classification of Diseases 10th revision (ICD-10) diagnosis code X60-X84 (suicidal behaviour of known intent) and Y10-Y34 (suicidal behaviour of unknown intent).^24 25^ Only diagnoses made in specialist care are considered as our data linkage does not include primary care diagnoses.

We will consider suicide attempts or death by suicides (suicidal behaviour) within 30 days of SSRI initiation. As secondary analyses, we will (a) consider only suicidal behaviour of known intent within 30 days, and (b) consider suicidal behaviour within 90 days of SSRI initiation.

### Predictors

#### Broad predictor model

We will include a broad range of predictors based on the availability in our register linkage.

The predictors include: sex; age at SSRI initiation; history of mental and behavioural disorder diagnoses, previous suicidal behaviour and overdoses; psychotropic medications; highest commenced education between the index person and their parents in the year before SSRI initiation; prescriber practice type; parental history of mental and behavioural disorder diagnoses, suicidal behaviour and overdoses (same codes as in individuals); and family history of death by suicide. See tables 1 and 2 for diagnosis definitions, and table 3 for medication definitions.

**Table 1 T1:** Predictors included in the broad predictor model, by register

Total population register	
Sex	
Native born	
National patient register	
Psychiatric diagnosis within 3 months before initiation	See table 2 for diagnosis subdivisions.
Psychiatric diagnosis >3 months before initiation	
Prescribed drug register	
Age at initiation	1 year bands.
Prescriber practice	Primary/specialist/psychiatric specialist.
Psychiatric drug receipt within 3 months before initiation	See table 3 for medication subdivisions.
Psychiatric drug receipt >3 months before initiation	
LISA	
Highest commenced education of index individual’s parents	Primary school, secondary school, university/vocational school.
Multigeneration register+national patient register	
Family history of psychiatric disease among the index individual’s parents: lifetime before initiation	See table 2 for diagnosis subdivisions.
Multigeneration register+cause of death register	
Family history of death by suicide among index individual’s parents: lifetime before initiation	All ICD-10 X60-X84; Y10-Y34.

ICD-10, International Classification of Diseases, 10th revision; LISA, Longitudinal Integrated Database for Health Insurance and Labour Market Studies.

**Table 2 T2:** Diagnoses codes included for predictors

Diagnosis	ICD-10 code categorisation
Mental and behavioural disorders	
Organic mental disorder	F00-F09
Substance use disorder	F10-19
Schizophrenia and psychotic disorder	F20-F29
Manic episode	F30
Bipolar disorder	F31
Depression	F32, F33
Persistent mood disorder	F34
Other or unspecified mood disorders	F38, F39
Phobic anxiety disorder	F40.0-F40.2
Other anxiety disorders	F41.0-F41.1
OCD	F42
Reaction to severe stress, and adjustment disorders	F43
Anorexia nervosa	F500, F501
Bulimia nervosa	F502, F503
Non-organic sleep disorders	F51
Dissocial personality disorder or emotionally unstable personality disorder	F602, F603
Gender identity disorders	F64
Mental retardation	F70-F79
Autism	F840, F841, F845, F848, F849
Hyperkinetic disorder	F90
Conduct disorders	F91
Suicidal behaviour	X60-X84, Y10-Y34
Overdose	T36-51, X40-49

ICD-10, International Classification of Diseases, 10th revision; OCD, Obsessive-Compulsive Disorder.

**Table 3 T3:** ATC codes included for predictors

Medication	ATC code
Opioids and pain medication	N02A
Antiepileptic drugs	N03A
Antipsychotics	N05A
Anxiolytics, hypnotics and sedatives	N05B excluding N05BA, N05C
Benzodiazepines	N05BA
Antidepressants, excluding SSRIs	N06A excluding N06AB
ADHD medication	N06B
Drugs used in addiction disorders	N07B

ADHD, attention deficit hyperactivity disorder; ATC, Anatomical Therapeutic Chemical; SSRI, selective serotonin reuptake inhibitor.

All predictors aside from age will be considered as categorical variables. If there is evidence for it, we will consider accounting for non-linear effects of age in the elastic net logistic regression (EN) model.

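### The open-ended drug and outpatient history predictors look back further in the testing sample than in the training sample, so register length is mixed into the temporal calibration check

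*Protocol article*

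**What the plan says.** Table 1 (Predictors, Broad predictor model) splits drug history in two: "Psychiatric drug receipt within 3 months before initiation" and "Psychiatric drug receipt >3 months before initiation". Psychiatric diagnoses are split in the same way. The second window has no outer limit.

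The Data source section gives the register dates. The Prescribed Drug Register is described as one "which includes all dispensed medications since July 2005", and the National Patient Register as "documenting discharge diagnoses from inpatient and outpatient care since 1973 and 2001, respectively".

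The Inclusion criteria admit people aged 8 to 24 "who were born in Sweden and who initiated an SSRI after a wash-out period of 365 days free from any antidepressants", with initiations from 1 January 2007 to 31 December 2020.

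Model development splits the data by calendar time: 2007-2017 for training and 2018-2020 for testing. No section caps the look-back, makes it equal across the two samples, or adjusts for calendar year.

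**The concern.** A yes/no variable for any receipt more than three months ago depends on how much register lies behind the person. Here that length is set by the calendar date of initiation, and the training/testing split is also by calendar date. The same column therefore measures a short history in much of training and a long one throughout testing.

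Two things follow. In training, some people with a true history are recorded as having none, so the contrast between history and no history is diluted. In testing, more people are recorded as positive even if nothing has changed, so the model adds risk that it had already absorbed into its no-history group.

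The temporal split is the plan's main validation. It is judged by a calibration plot, the Brier score and performance at a 1% risk threshold, and the Generalisability section relies on it for stability over time. A shift caused by register length could be misread as a real change in the population or as poor transportability.

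**Working it through.** The plan states no look-back length, so there is no figure of its own to reproduce. The check is date arithmetic followed by an illustration.

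**1. Drug window.** Register start July 2005 (taken as 1 July); initiation dates from the Inclusion criteria.

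Window = (initiation date − 1 July 2005) − 3 months.

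| Initiation | Register time | Window beyond 3 months |
|---|---|---|
| 1 Jan 2007 | 18 months | 15 months (1.25 y) |
| 31 Dec 2007 | 30 months | 27 months (2.25 y) |
| 31 Dec 2017 | 150 months | 147 months (12.25 y) |
| 31 Dec 2020 | 186 months | 183 months (15.25 y) |

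Training covers 1.25-12.25 years and testing 12.25-15.25 years; before the age limit the ranges meet only at the boundary. The range from first to last entrant is 15.25 / 1.25 = 12.2-fold.

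**2. Age limit.** The window cannot exceed age minus 3 months. At the end of 2020 it is 7.75 years at age 8, 11.75 at age 12, 14.75 at age 15, and the full 15.25 from age 16. If initiations were uniform over date and age (assumed), the mean window would be about 6.7 years in training and 12.7 in testing.

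**3. Diagnoses.** Outpatient records from 2001 (taken as 1 January) give 5.75 years on 1 January 2007, 16.75 at the split and 19.75 at the end of 2020, a 19.75 / 5.75 = 3.4-fold range. Inpatient records from 1973 predate the birth of every entrant: the oldest, aged 24 on 1 January 2007, was born in 1982 or later. They do not drift.

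**4. Illustration for one drug predictor.** Assumptions, none from the plan:
- first exposure at a constant rate h of 1-5% per year from age 8
- relative risk RR of 2-4 that does not fade
- no repeat exposure
- initiations uniform over time
- true risk 1% in both periods (the plan's approximate 30-day prevalence)

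Let T = age − 8 − 0.25 years and L = drug window.
- True history: p = 1 − exp(−hT)
- Recorded history: mean of 1 − exp(−h·min(L, T)) over each period, giving q_train and q_test
- Risk without history: r0 = 0.01 / (1 + p(RR − 1)); with history: r1 = RR·r0
- Risk in training among those recorded as having none: ru = (0.01 − q_train·r1) / (1 − q_train)
- Mean predicted risk in testing: E = q_test·r1 + (1 − q_test)·ru; observed/expected = 0.01 / E

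Age 20 (T = 11.75), the two ends of the range:
- h = 1%, RR = 2: p = 0.111, q_train = 0.065, q_test = 0.111; r1 = 0.0180, ru = 0.00945; E = 0.0104; observed/expected 0.96, inflation 4%.
- h = 5%, RR = 4: p = 0.444, q_train = 0.277, q_test = 0.444; r1 = 0.01715, ru = 0.00726; E = 0.01165; observed/expected 0.86, inflation 17%. The relative risk learned in training is 0.01715 / 0.00726 = 2.4 instead of 4.

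The same formula at other ages gives an inflation of 0.3-2.4% at age 12, 0.8-6% at 14 and 1.7-10% at 16. At age 24 it is 5-17%, much as at 20.

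**5. Constant predictors.** Table 1 lists native birth, yet eligibility requires birth in Sweden, and the Data source section takes birth country from the index individual. Crossing Table 1's three-month window with Table 3's class "Antidepressants, excluding SSRIs" gives a cell that is empty by design, because three months lies inside the 365-day wash-out. Beyond three months the class is usable, but only past 12 months: 18 − 12 = 6 months of register on 1 January 2007 and 186 − 12 = 174 months (14.5 years) at the end of 2020.

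**The case against.** **An all-available look-back is a legitimate choice.** It uses more information, and a short window discards real history. This stands as a trade-off, and it rules out a six-year cap on all diagnoses. Such a cap would throw away inpatient data that are complete for every entrant and that feed previous suicidal behaviour, one of the three predictors fixed in advance for the restricted model. It does not justify a window whose length differs systematically between training and testing.

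**The plan would notice the problem.** The calibration plot and Brier score would show miscalibration, and the plan notes that the elastic net intercept can be changed to fit a population. That is true, but neither identifies the cause, and changing the intercept does not restore a diluted coefficient.

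**The size depends on assumptions.** This stands. The effect is small in children. It would shrink if the relative risk fades with time or if people are treated repeatedly. No effect on AUC has been shown, and AUC governs tuning and selection; all candidate models share the same predictors.

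**The full protocol might set a cap.** It might. But Table 1 does fix windows: it states three months for the short one and lifetime for parental history, and leaves this one open.

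**Stronger readings that a reader might infer.** The open window does not contradict the register dates; it is a badly fixed definition. A window of about 15 years in 2020 does not apply to everyone, since age is the limit below about 16. The two constant predictors do conflict with eligibility, but a constant column carries no information and biases nothing. Finally, one might hold that the strengths statement ("covering virtually any Swedish resident who initiated selective serotonin reuptake inhibitor treatment during the study period") is contradicted by excluding foreign-born residents. It can equally be read as describing the data linkage, and the article draws no stated conclusion about foreign-born residents, so that point is not made here.

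**Conclusion.** The point holds for drug receipt and, to a lesser degree, for outpatient diagnoses. It does not hold for inpatient diagnoses. The unequal windows follow directly from the plan's own dates (day of register start assumed).

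Their consequence is a matter of degree. Under the assumptions above, one drug predictor would inflate mean predicted risk in testing by about 4-17% at age 20 and about 0.3-2.4% at age 12, with no true change in risk. The overall effect depends on the age mix and on how many such predictors the model uses, which the article does not give.

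This does not invalidate the study or its discrimination results. It does mean that calibration over time, as planned, cannot separate a longer register from real drift. The definition should be settled before the models are fitted.

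**What to change.** 1. Define drug-receipt and outpatient-diagnosis history over one look-back that every entrant has, identical in training and testing. Examples are months 3 to 18 for drugs (complete from 1 January 2007) and 3 months to about 6 years for outpatient diagnoses.
2. Keep inpatient history, including previous suicidal behaviour recorded in inpatient care, over the full available period.
3. Report test-period AUC and calibration under both the common and the unlimited look-back. Miscalibration that remains under the common window cannot come from register length.
4. Tidy-up with no effect on results: reconcile the native-birth row with the eligibility rule, and remove the empty cell for non-SSRI antidepressants within three months.

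**Cost.** Variables are re-derived from data in hand, and the models are fitted a second time for the comparison. Older drug and outpatient history goes unused in the common-window version. With months 3 to 18 and the wash-out, non-SSRI antidepressants would be informative only in months 12 to 18. Reporting the unlimited version alongside shows what this loses.

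### Table 2 labels a predictor as other anxiety disorders but codes only F41.0-F41.1, so F41.2-F41.9 diagnoses enter no predictor

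*Protocol article*

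**What the plan says.** The Predictors section, under Broad predictor model, sets the ambition: "We will include a broad range of predictors based on the availability in our register linkage". The diagnosis predictors are described without restriction as "history of mental and behavioural disorder diagnoses, previous suicidal behaviour and overdoses", and the reader is sent to the tables for their content: "See tables 1 and 2 for diagnosis definitions, and table 3 for medication definitions". Table 1 lists psychiatric diagnoses in two windows for the individual (within 3 months and more than 3 months before initiation) and lifetime for the parents, and points onward: "See table 2 for diagnosis subdivisions". For parents the text specifies the "same codes as in individuals".

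Table 2 then fixes the anxiety row as "Other anxiety disorders F41.0-F41.1". For mood disorders it has a row headed "Other or unspecified mood disorders", coded F38 and F39. The coding rule is "All predictors aside from age will be considered as categorical variables".

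**The concern.** The row's label names a wider group than its codes. Someone with F41.2, F41.3, F41.8 or F41.9 and no F41.0 or F41.1 sits at the reference level of a predictor whose name describes them.

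Two things are at stake:

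- **Lost information.** The National Patient Register supplies the diagnosis predictors (Data source section). The omitted codes come from the same register, so availability does not explain leaving them out.
- **Use of the score.** The Restricted predictor model section under Model development expects clinicians to calculate scores from reported coefficients, possibly through an online tool. The Generalisability section relies on standard ICD-10 definitions so that other countries can find comparable predictors. If this predictor reaches the final model, a user who reads only the label would tick it for a patient with unspecified anxiety, although the coefficient was estimated with such patients coded negative. Internal validation cannot reveal this mismatch, because training and testing use the same coding.

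**Working it through.** The plan states no figure on this point, so there is none to reproduce. The check has two parts.

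**1. Coverage of Table 2.** Each Table 2 row with F codes was placed on a grid from F00.0 to F99.9.

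- Rows with F codes: 21. No two overlap.
- F41: .0 and .1 are listed; .2 to .9 are in no row.
- Other partly covered categories: F40 (.0 to .2 listed), F50 (.0 to .3), F60 (.2 and .3) and F84 (.0, .1, .5, .8, .9).
- Number ranges with no row: F35-F37, F44-F49, F52-F59, F61-F63, F65-F69, F80-F83, F85-F89 and F92-F99. Some of these numbers may be unused in ICD-10.
- Residual rows: mood has one (F38, F39). Anxiety has none, and no row covers any other F code.

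The protocol shows only that no row holds an F41 code above .1. That those codes include mixed and unspecified anxiety comes from the ICD-10 classification the protocol adopts, not from its text.

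Example: a person's only specialist diagnosis is F41.9, recorded two months before initiation. The other-anxiety predictor is 0 for the recent window, and every other Table 2 diagnosis is also 0. The same happens in the earlier window or for a parent.

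**2. What this could mean in numbers (illustration only).** Let p be the proportion of the cohort with any F41 code, and s the share of them coded only outside .0 and .1. Both are assumptions.

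- Flagged by the predictor: p(1 − s).
- Proportion c of the unflagged who do carry an F41 code: c = ps / [1 − p(1 − s)].

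With p = 0.20:

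| s | Flagged | c |
|---|---|---|
| 0.25 | 0.15 | 0.05 / 0.85 = 5.9% |
| 0.50 | 0.10 | 0.10 / 0.90 = 11.1% |
| 0.75 | 0.05 | 0.15 / 0.95 = 15.8% |

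Now let R1 be the risk ratio for F41.0-F41.1 and R2 that for the unlisted F41 codes, both against people without F41. The contrast the predictor shows is R1 / [1 + c(R2 − 1)].

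- R1 = R2 = 2: 2/1.059 = 1.89, 2/1.111 = 1.80, 2/1.158 = 1.73.
- R1 = 2, R2 = 1: 2.00 at every s.

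So attenuation depends on the risk under the unlisted codes, which the documents do not give.

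**The case against.** The best defence is that Table 2 is selective throughout. It picks subcodes in F40, F50, F60 and F84, and a broad range of predictors is not a promise of every F code. A prediction model need not cover the whole chapter, and the codes as printed are explicit and reproducible. The article is also condensed, so a rationale may sit in a fuller document. This has force for rows whose labels are as narrow as their codes. A reader might infer that the eating-disorder and personality rows are also errors. The documents do not support that: those rows name specific disorders and look like deliberate choices. The defence does not rescue the F41 row, where the printed label and the printed codes disagree whatever the rationale.

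Three further objections stand and limit the point:

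- **Other predictors still carry information.** A reader might infer that these patients are treated as having no psychiatric history. That goes too far: prescriber practice, psychiatric drugs in two windows, other diagnoses and parental history all remain. The reference group was also never free of disorder. Everyone in it started an SSRI, and the Outcome ascertainment section says the linkage holds no primary care diagnoses.
- **Bias toward no effect is not shown.** A reader might infer that the anxiety coefficient must shrink. That requires raised risk under the unlisted codes, and even at equal risk the illustration gives a modest change.
- **Loss from the restricted model is not shown.** Tables 1 to 3 give about 91 predictors (23 × 3 diagnosis rows + 8 × 2 drug rows + 6 others). The top 30 from each of four base models are pooled and then judged on clinical input and evidence. Nothing in the documents shows that anxiety would miss that pool.

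It could also be said that Table 1 implies a flag for any psychiatric diagnosis. None is defined; its rows refer to the Table 2 subdivisions. If one is intended, it should be stated.

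**Conclusion.** The point holds for the F41 row and for the absence of a residual F row. Followed as written, the models ignore F41.2-F41.9 diagnoses already in the linkage. This occurs in three predictor sets (recent, earlier, parental), under a label that covers those diagnoses, while mood disorders get a row for the unspecified remainder.

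The size cannot be fixed from the documents. The 5.9% to 15.8% range rests on an assumed 20% F41 prevalence and assumed shares of 25% to 75%; it is not an estimate for this cohort. Internal validation is not biased. The consequences that can be defended are some loss of available predictive information and a label that can be misapplied when the score is used by clinicians or abroad.

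**What to change.** In Table 2:

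1. Keep F41.0-F41.1 as its own row, under a label that matches those codes.
2. Add a row *Mixed, other or unspecified anxiety, F41.2-F41.9*. Keep it separate, because risk may differ and a single F41 row could blur the predictor.
3. Add one residual row *Any other F code not listed*. This picks up the remaining codes without altering the narrowly labelled rows.

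Apply both new rows to the individual in both windows and to the parents.

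Cost: a code-list edit before extraction, with no new data. Two rows in three sets give 2 × 3 = 6 more binary predictors, taking about 91 to about 97, which the planned shrinkage and cross-validated tuning can handle. If the authors prefer to leave F41.2-F41.9 out, the row should at least be relabelled and the reason given.
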